After at least 30 min in the classroom, the observer rates 10 items on a Swedish translation of the Classroom Atmosphere Measure. Using behavioral indicators, items are rated on a scale of 1–4, with the option of scoring 0 if the item is not possible to rate or not applicable. A previous study measured internal consistency at α = 0.92 and kappa coefficients ranging from 0.62 to 0.81 (44).

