### Data analysis

2.5.

As this study aims to investigate the effects of introducing GBG under real-world circumstances, whether the sample is compliant to the intervention or not, data analysis of the primary and secondary outcomes will follow intention-to-treat (ITT) procedures. The primary objective can be described as the difference in change over time in conduct problems between the group receiving GBG and the group receiving BAU. This can be expressed as a general linear model where conduct problems would signify the primary outcome of interest (denoted as 
Y
), with intervention group, time, and stratification variable (sociodemographic index score) being converted to dummy-scores and denoted as 
$\beta_{1}$
, 
$\beta_{2}$
, and 
$\beta_{3}$
 respectively, using an interaction term (
$\beta_{1}\times \beta_{2}$
) for intervention group and time. This approach entails some statistical considerations. One consideration is adjusting for the standard errors being affected by clustering (45). Since the municipality only has capacity to implement GBG in a low number of schools, considerations have to be made regarding the degree of precision in statistical models with few clusters. One option is to use a Bayesian ITT-model, which could render more precise estimates compared to corresponding frequentist models as long as default naïve priors aren’t used (46). Data for priors may be limited, particularly for some of the secondary outcomes, in which case weakly informed priors will be used. The estimates can also be compared with the corresponding frequentist ITT-analysis. As priors can have notable effect on estimates (47), sensitivity analyses will be conducted.

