Analyses for secondary outcomes, including observational measures, will in large follow similar procedures, i.e., as outcomes in linear univariate models. Statistical analyses related to implementation will be treated differently. To assess implementation as a moderator, a parameter for procedural fidelity will be added to the statistical model for the primary analysis. Note that this is contingent on the chosen proxy for implementation to have some degree of variation. An earlier study reported high procedural fidelity across the board, with only dosage being suboptimal (21). This indicates that dosage may be a more potent moderator to investigate compared to procedural fidelity. Due to the previously mentioned difficulties in collecting data on dosage, the teacher-rated variable for number of GBG-sessions last week may be used as a proxy for dosage instead of the trainer-collected data on number of GBG-sessions for the school year.

While all data collection is handled by employees who have the same or similar formal requirements, the theoretical requirements of data “missing completely at random” are high. It is also possible that data could be “missing at random”, but in this case there are many unobserved variables that could potentially explain systematic differences between missing and observed data. Should missing data occur, it will primarily be assumed as “missing not at random”. Consequently, listwise deletion will be the default option to handle missing data. Multiple imputation will also be considered in cases where arguments can be made for data being missing at random, or where inclusion of auxiliary variables is deemed suitable. However, no measured variables in this study are currently expected to predict or correlate with potential missing data.

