The lack of restrictions in this pragmatic trial also increases the importance of tracking behavioral management practices in the control group. Usual care or practice has a history of only being vaguely defined and controlled for (52). The efficacious behavioral management practices found in GBG could potentially be more widely disseminated among teacher staff in this sample compared to previous studies, e.g., due to generally increased knowledge or teacher mobility within the municipality. To address this, behavioral management practices will be tracked in both groups by independent observers and teacher-rated measures.

The study design poses some methodological considerations, most notably the reduction in statistical power by the limited sample size and classroom-level variables. An earlier version of the study used individual-level variables (with a corresponding three-level power analysis) in conjunction with consent forms where parents could actively opt-out their children from the data collection, similar to the design used by the English GBG-trial (53). However, the Swedish Ethical Review Authority required active consent from all parents. This prompted a change in design to remove individual-level variables as there were major concerns with attrition using active consent forms, particularly in areas with lower socio-economic status. Further, any potential changes had to be made rapidly as preparations and implementation of GBG need to be timed accordingly to the school year, and the pool of local eligible schools is expected to reduce for each implementation cycle. This also precluded the inclusion of an updated power analysis corresponding to the new design and pre-registering the study before recruitment. This limitation should be considered in light of the difficulties in achieving suitable sample sizes in highly pragmatic conditions. A potential benefit is that the current design is relatively low-cost and lightweight, making it suitable for pragmatic aims. This may encourage more trials when organizations import or develop interventions before scaling up, which could be a significant investment considering each trainer require at least three years of development in this case. Newer interventions may however still need large trials under ideal conditions to first determine efficacy.

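### Data are assumed missing not at random and, on that ground, listwise deletion is made the default, which that assumption does not justify

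*Protocol article*

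**What the plan says.** All of this stands under Data analysis (2.5) in the protocol article. The paragraph on missing data first notes that the MCAR requirements are high. It then allows that data could be MAR but points to many unobserved variables, and settles on a working assumption: "Should missing data occur, it will primarily be assumed as “missing not at random". The rule comes next: "Consequently, listwise deletion will be the default option to handle missing data". Imputation is a discretionary alternative: "Multiple imputation will also be considered in cases where arguments can be made for data being missing at random", or where auxiliary variables seem suitable. The paragraph ends by saying that "no measured variables in this study are currently expected to predict or correlate with potential missing data".

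Earlier in the section, the primary objective is the between-arm difference in change in conduct problems, modelled with arm, time, stratum and an arm-by-time interaction. The only sensitivity analyses named are about priors: "As priors can have notable effect on estimates (47), sensitivity analyses will be conducted".

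**The concern.** The mechanism assumed and the method chosen do not fit each other. If missingness depends on unobserved values, the complete cases are a selected subset, and restricting the analysis to them does nothing about the selection. Doubting MAR is a reason to ask how far the result could move under plausible departures from it. It is not a reason to fall back on a method that in general needs MCAR or purely covariate-dependent missingness.

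The primary contrast is at stake. The outcome is rated by unblinded teachers, as the Discussion acknowledges, and in the intervention arm the rater also delivers the programme. Non-return that differs between arms is therefore plausible. The Discussion also expects smaller effects, so a bias of around a tenth of an SD would not be negligible. Data collection is complete according to Trial status, so a later choice between deletion and imputation could be made with the missingness pattern already visible.

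**Working it through.** The plan gives no figure to reproduce: it states no expected missing rate, outcome SD or between-wave correlation. The check is a comparison of statements, followed by an illustration.

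**Statements set side by side.** (1) MCAR is demanding. (2) Missing data are taken to be MNAR. (3) Therefore delete listwise. Step 3 would need MCAR, which step 1 doubts, or missingness explained by model covariates, which step 2 sets aside. Imputation is optional and MAR-based, and the closing statement that no measured variable predicts missingness removes most of its rationale.

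**Illustration: assumptions, none from the documents.** Outcome SD 1 at each wave; T1–T3 correlation ρ = 0.6; T1 complete; 20% or 30% missing at T3; missingness logistic in either the T1 or the T3 score. Clustering is ignored because only bias is examined. *Listwise* here means that a classroom without T3 contributes nothing.

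**Formula.** Let m be the mean, among observed classrooms, of the score that drives missingness. The full-sample mean is 0, and m is negative when high-problem classes go missing. Listwise bias in one arm's mean change is

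- missingness on T3: E[T3 | obs] − E[T1 | obs] = m − ρm = (1 − ρ)m
- missingness on T1: ρm − m = −(1 − ρ)m

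With a logistic slope of 1 per SD, m is −0.173 at 20% missing and −0.253 at 30%. With ρ = 0.6 this gives 0.4 × 0.173 = 0.07 and 0.4 × 0.253 = 0.10 in absolute value. Large-sample simulation agrees:

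| Missingness (slope 1) | Missing at T3 | Listwise bias | MAR-type bias |
|---|---|---|---|
| On T1, intervention arm only | 20% / 30% | +0.07 / +0.10 | 0 / 0 |
| On T3, intervention arm only | 20% / 30% | −0.07 / −0.10 | −0.12 / −0.17 |
| On T3, opposite directions by arm | 20% / 30% | −0.14 / −0.20 | −0.23 / −0.34 |
| Same dependence and rate in both arms | 20% / 30% | 0 / 0 | 0 / 0 |

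Units are outcome SDs in the difference in change; negative values favour GBG. The sign reverses if the control arm is the one affected. The MAR-type estimator regresses T3 on T1, as a likelihood or imputation analysis in effect does.

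With slopes from 0.5 to 2 and missingness on T3 in one arm, listwise bias runs from −0.04 to −0.15 and MAR-type bias from −0.06 to −0.27. By the formulas, missingness on T1 gives the same absolute listwise range, while MAR-type bias stays at about zero.

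**Unit of deletion.** The article does not say whether deletion applies per classroom or per classroom-wave record. If per classroom, a missing T2 would also remove observed T1 and T3 scores. With an assumed 10% missing independently at each wave, 0.9³ = 0.729 of classrooms would remain, although 90% would have a T3 score. If per record, that loss does not occur.

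**The case against.** The strongest reply is that, under the plan's own MNAR assumption, a MAR analysis is no better. That stands. With missingness driven by T3, the MAR-type estimator was more biased than deletion in every one-arm setting examined, by a factor of about 1.6 to 1.8. Declining to make MAR imputation the default is therefore defensible, and a likelihood analysis alone is no cure. It does not follow that MNAR supports deletion: both are biased, and only an analysis that varies the unobserved scores shows by how much.

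A second reply is that time enters as a predictor, which suggests one row per classroom and wave, so that only the missing row would be lost. If the model also carries within-classroom correlation, the available-data analysis may already be close to what is intended. This too stands as a possibility, but the text does not settle it. A third is that bias cancels when mechanism and rate match across arms. That is true, but the plan does not assume it.

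Some stronger readings are tempting but unsupported:

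- *The rule discards randomised units and so breaks the commitment that* "data analysis of the primary and secondary outcomes will follow intention-to-treat (ITT) procedures". Schools are randomised, classrooms are measured, and the section explains ITT in terms of compliance.
- *The Discussion contradicts the claim about predictors of missingness by citing* "major concerns with attrition using active consent forms, particularly in areas with lower socio-economic status". That passage is about parental consent in an abandoned individual-level design, not teacher returns in the present one.
- *The observer scale's rule,* "with the option of scoring 0 if the item is not possible to rate or not applicable", *would delete whole observations.* Nothing says so, and scoring rules are ordinary SAP detail.
- *No MNAR analysis exists.* The article names none; a SAP, which is not shown, might.

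**Conclusion.** The point holds as a fault in what the article fixes: MNAR is given as the reason for a default that it does not justify, and the sensitivity analyses named do not address missing data. Under the assumptions above, and if classrooms without T3 are dropped, the illustrative bias is about 0.04–0.15 SD with 20–30% missing in one arm. It would be larger if the arms lose opposite kinds of classroom, and about zero if they lose the same kind at the same rate. The direction cannot be known in advance.

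This should be corrected before analysis. It is not shown to be critical, because no expected missing rate is documented and with little missing data the effect would be small.

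**What to change.** Before the data are analysed:

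1. Replace the listwise default with a mixed or Bayesian likelihood that uses all observed classroom-by-wave scores, models within-classroom correlation and includes the stratum. State that this is valid under MAR and does not correct for MNAR.
2. Add, as the essential MNAR component, a delta-adjusted or tipping-point analysis that shifts missing T3 scores in one arm at a time and then in both. Fix the range in advance (for instance 0 to +0.5 SD, towards more conduct problems) and report where the conclusion changes.
3. Report complete cases as a sensitivity analysis only, and say whether deletion there is per classroom or per record.
4. Remove, or justify, the sentence that no measured variable is expected to predict missingness.

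The cost is a change of wording and one additional sensitivity table. No new data are needed.

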## Discussion

3.

The current trial will evaluate the effects of GBG compared to BAU, primarily using teacher ratings and blinded observer ratings across three time points during a school year. As previous trials have demonstrated efficacy for GBG, this trial places larger focus on effectiveness or pragmatic aims, along with testing the transportability of GBG. The pragmatic focus means that allocations mirror real-world conditions as closely as possible, with the research group trying to minimize restriction and its own impact regarding all aspects of school practice in the trial. This should add to the literature concerned with moving GBG along a translational research pipeline (48, 49). Also concerning translational research, the study should be able to partially apply findings within the RE-AIM framework (50), which focuses on the reach, effectiveness, adoption, implementation, and maintenance of public health interventions. Some key variables for assessing these areas are the number of students exposed to the intervention, number of teachers providing GBG, their level of fidelity, and whether teachers expect to continue their use of GBG. Should these parameters be favorable, even smaller effect sizes could be valuable from a public health perspective.

Smaller effect sizes may be expected as this study employs a parallel group design with observer-rated measures taking place strictly outside game sessions. Although the teacher-rated measures should take behaviors both in and outside GBG-sessions into consideration, moderate to large effect sizes for GBG are more common in single-case experimental designs using observational measures while the game is played (51). A benefit with the current design is that it allows investigation of whether behaviors generalize across time and context when implementing GBG, e.g., if conduct problems are reduced in classrooms as well as common school areas, or whether potential effects are immediate and transient, rather than sustained over the school year.

The lack of restrictions in this pragmatic trial also increases the importance of tracking behavioral management practices in the control group. Usual care or practice has a history of only being vaguely defined and controlled for (52). The efficacious behavioral management practices found in GBG could potentially be more widely disseminated among teacher staff in this sample compared to previous studies, e.g., due to generally increased knowledge or teacher mobility within the municipality. To address this, behavioral management practices will be tracked in both groups by independent observers and teacher-rated measures.

The study design poses some methodological considerations, most notably the reduction in statistical power by the limited sample size and classroom-level variables. An earlier version of the study used individual-level variables (with a corresponding three-level power analysis) in conjunction with consent forms where parents could actively opt-out their children from the data collection, similar to the design used by the English GBG-trial (53). However, the Swedish Ethical Review Authority required active consent from all parents. This prompted a change in design to remove individual-level variables as there were major concerns with attrition using active consent forms, particularly in areas with lower socio-economic status. Further, any potential changes had to be made rapidly as preparations and implementation of GBG need to be timed accordingly to the school year, and the pool of local eligible schools is expected to reduce for each implementation cycle. This also precluded the inclusion of an updated power analysis corresponding to the new design and pre-registering the study before recruitment. This limitation should be considered in light of the difficulties in achieving suitable sample sizes in highly pragmatic conditions. A potential benefit is that the current design is relatively low-cost and lightweight, making it suitable for pragmatic aims. This may encourage more trials when organizations import or develop interventions before scaling up, which could be a significant investment considering each trainer require at least three years of development in this case. Newer interventions may however still need large trials under ideal conditions to first determine efficacy.

An additional consideration is that the primary outcome is teacher-rated and not blinded. This is only partially addressed using blinded and independent observers as they only observe a subset of classrooms due to financial limitations, specifically one classroom for each grade in each school. The blinded measures will still serve an important role in corroborating teacher-rated outcomes, with discrepancies between observer-rated and teacher-rated measures potentially implying weaker effectiveness. For example, positive changes in teacher-rated measures, but not in observer-rated measures, could potentially imply rater bias or that changes in behavior have not generalized outside of game sessions. Another possible limitation is that the study assesses change in multiple outcomes, meaning multiple independent comparisons. This could potentially increase the risk of type I error but should be ameliorated by having pre-specified a primary outcome, primary endpoint, and methods for data analysis. The breadth of outcomes also allows for the evaluation of more positive goals. For example, conduct problems could in theory be suppressed by using highly aversive or restrictive methods, but such methods would likely have detrimental effects on other outcomes assessed in this study.

In conclusion, this trial should inform the literature on how an adapted version of GBG fares in a naturalistic scenario. This has implications for how preventive interventions with high reach can be disseminated and adopted in order to reduce the risk factor of early conduct problems.

## Ethics and dissemination

4.

The study has been approved by the Swedish Ethical Review Authority (2020–06804). As the allocations consist of either a previously tested intervention or usual practice, the trial is deemed to pose minimal risk to participants. Forms for informed consent have not been used as the trial will not collect personal or sensitive information. Data will still be collected through or in conjunction with locked systems, only accessible by the research group, for interim storage. All raw data will then be stored on a secure platform (LUSEC) with access restricted to the PI and data manager.

The trial results will primarily be disseminated through two manuscripts: One manuscript will detail results regarding research questions centered on changes in primary and secondary outcomes. This manuscript will report according to CONSORT 2010 Statement (54). The other manuscript will focus on research questions regarding implementation. This study protocol is reported according to SPIRIT-guidelines (55), see Supplementary Table S2 for a SPIRIT Checklist with additional details.

## Trial status

5.

The trial has currently completed data collection. Any other major updates, amendments or revisions regarding the trial will be reported to this journal and ClinicalTrials.gov. As the trial has currently completed phases requiring participant involvement, any new amendments are not expected to require further reviewing by the Swedish Ethical Review Authority. Though should such amendments occur, they will be reported to relevant parties.

The current protocol version in use is 3.0 (dated 3 May 2023). Major changes from version 2.0 (dated 14 January 2021) to 3.0 include: Clearly specifying primary outcome and endpoint, changing from constrained to stratified randomization, reducing the number of classrooms observed by independent and blinded observers, removing old power analysis, and specifying details according to SPIRIT-guidelines. Major changes from version 1.0 (dated 16 June 2020) to version 2.0 include: removing individual-level measures.

## Ethics statement

The studies involving humans were approved by Swedish Ethical Review Authority. The studies were conducted in accordance with the local legislation and institutional requirements. Written informed consent for participation was not required from the participants or the participants’ legal guardians/next of kin because the trial does not collect personal or sensitive information.
